#### 2) Vital signs and laboratory tests

The results were analyzed by Chi-squared test, Fisher's Exact test, or Poisson test for each group of 12-lead ECG abnormalities at each time point. A summary statistic is presented and, if necessary, GLM or GLMM methods are used to perform group comparisons.

## [16] Evaluation Criteria of Safety Including Side Effects, Evaluation Method and Reporting Method

### 16.1 Adverse events evaluation

The adverse reaction is closely observed from the time of administration of the drug, and it is confirmed through consultation with the examiner during the visit and after consultation with the investigator. The date and date of the adverse reaction, the degree and the result of the adverse reaction, Details of the causal relationship with the measure and the Investigational Product, the name of the suspected drug other than the Investigational Product, the treatment and the treatment of the adverse reaction. In the event of an adverse reaction, the researcher should be informed immediately, and the clinical trial subject should be trained so that the patient can receive medical treatment. The evaluation, recording and treatment of detailed adverse events is in accordance with section 16.3.

### 16.2. Predicted adverse events

No significant adverse events were observed in the preceding clinical trial.

### 16.3 Evaluation methods and evaluation criteria for adverse reactions such as self-elevation symptoms

Adverse events are any undesirable anatomy, physiological or metabolic lesions that occur during the test, regardless of whether they are associated with an Investigational Product, or changes in somatic symptoms, signs, or clinical signs. These include worsening of existing conditions, comorbidities, and drug interactions.

In this clinical study, when the clinical results of the visit 2 were beyond the normal range of the experimental test, the vital sign measurement, and the electrocardiogram, the investigator judged the clinical significance of the result, Adverse events were reported with findings. It is the responsibility of the person responsible for the clinical trial to document any adverse events that occur during clinical trials. Adverse events should be recorded in medical diagnostic terms and, if this is not possible, be observed by the investigator or the person responsible for the clinical trial, or recorded the terms of the symptoms and signs reported by the subject.

The case record records the symptoms and signs of the adverse reaction, duration (start and end date), severity, causal relationship with the drug for the clinical trial, measures taken in relation to the adverse reaction.

1) Severity of adverse events

The severity of the adverse events is assessed in five grades of Grade 1 to 5 according to CTCAE v4.0, but Grade 4 or 5 is considered a serious adverse event. The following is a generic example of CTCAE v4.0.

| 1 = Mild | Asymptomatic or mild symptoms: Only routine or diagnostic observation is possible. Therapeutic intervention is not required |
| --- | --- |
| 2 = Moderate | Minimal, local, or non-invasive treatment is needed: routine activities such as meal preparation and shopping |
| 3 = Severe or medically significant but not immediately life-threatening) | Severe, medically significant, or not immediately life threatening: limited self-care activities such as bathing, dressing, meals, toiletries, etc., without hospitalization or extension of length of stay |
| 4 = Life-threatening consequences) | Immediate treatment is required |
| 5 = Death related to AE | Death-related adverse events |

2) Causality with Investigational Product

When an adverse reaction occurs, the investigator classifies the investigator as follows and records his or her opinion on whether or not it is related to the investigational product.

| Evaluation step | Evaluation standard |
| --- | --- |
| Certain | If the relationship between drug administration and adverse events is reasonable  If the adverse event is not explained by other medicines, chemicals or accompanying diseases  Clinically appropriate response at discontinuation  Re-administration (if possible only) is pharmacologically or phenomenologically critical |
| Probable/Likely | If the temporal relationship between drug administration and adverse events is reasonable  If the adverse event does not appear to be due to other medicines, chemicals or accompanying diseases  Clinically appropriate response at discontinuation  If there is no re-admission information |
| Possible | If the temporal relationship between drug administration and adverse events is reasonable  If the adverse event is also explained as being caused by other medicines, chemicals or accompanying diseases  Insufficient or unclear information about discontinuation |
| Unlikely | In the case of transient cases in which there is no likely causal relationship between drug administration and adverse event manifestations  If the adverse reaction is due to other medicines, chemicals or potential disease. |
| None | If an adverse reaction occurs without drug administration  If the adverse events that occurred before drug administration did not deteriorate after administration |
| Conditional/Unclassified | If you need more material or are reviewing additional material for proper evaluation |
| Inaccessible /Unclassifiable | Incomplete or conflicting information and can’t be determined or supplemented or confirmed |

3) Actions taken in relation to adverse events

| 0 = No action taken |
| --- |
| 1 = Study drug dosage adjusted / temporarily interrupted |
| 2 = Study drug permanently discontinued due to this adverse event |
| 3 = Concomitant medication taken |
| 4 = Non-drug therapy given |
| 5 = Hospitalization / prolonged hospitalization |

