#### 1) Adverse events

Summarize the adverse events observed following administration of the investigational product. The number of cases and the number of patients who experienced an adverse reaction, abnormal drug response, SAE, death, adverse events n that caused discontinuation of clinical trial, and / or "other significant adverse events (OAE) do. The number of subjects who received each of the abnormal responses was also summarized by body-organ system (SOC), recommended language, and maximum severity for each treatment group. In addition to the summary statistics, the incidence or incidence of adverse events in the group are analyzed using Chi-squared test, Fisher's Exact test, or Poisson test.

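### The Grade 3 severity descriptor excludes hospitalised events although its own heading does not, so a severe, hospitalised, non-life-threatening event may be graded inconsistently

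*Protocol*

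**What the plan says.** Section 16.3, item 1, names the scale: "The severity of the adverse events is assessed in five grades of Grade 1 to 5 according to CTCAE v4.0". It adds that Grades 4 and 5 count as serious adverse events. It then introduces its table: "The following is a generic example of CTCAE v4.0".

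Three rows of that table matter here:

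- Grade 2 descriptor: "Minimal, local, or non-invasive treatment is needed: routine activities such as meal preparation and shopping".
- Grade 3 heading: "3 = Severe or medically significant but not immediately life-threatening". The descriptor beside it broadly repeats the heading and then continues: "limited self-care activities such as bathing, dressing, meals, toiletries, etc., without hospitalization or extension of length of stay".
- Grade 4 heading: "4 = Life-threatening consequences". Its descriptor says only that treatment is needed at once.

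Hospitalisation appears in two other places. Item 3 of section 16.3 lists it among the actions taken: "5 = Hospitalization / prolonged hospitalization". Section 16.4 makes a hospital stay, or its extension, a criterion for a serious adverse event, separate from death or danger to life.

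The grade is used in section 15.3.6, item 1 (repeated in the Protocol Outline), where events are summarised by organ system, term and "maximum severity for each treatment group".

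**The concern.** A severity scale should give each event one grade. Here the two halves of the Grade 3 row disagree about an event the protocol clearly foresees, since it provides both an action code and a seriousness criterion for hospitalisation. The rater must choose between the heading and the descriptor, and the Protocol Outline lists six sites at which that choice will be made.

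Two things are at stake. The upper rows of the maximum-severity table may mix events graded on different readings. In addition, because Grade 4 is tied to seriousness, a rater who moves an admitted event up to Grade 4 records it as life-threatening when it was not. The clause brings a seriousness criterion, hospitalisation, into a severity definition.

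**Working it through.** No arithmetic applies. The check sets the table rows beside one another and passes typical events through them.

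**Does each row carry a hospitalisation condition?**

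- Grade 1: none.
- Grade 2: none.
- Grade 3 heading: none. Grade 3 descriptor: hospitalisation and prolonged stay are excluded.
- Grade 4: none. The heading requires life-threatening consequences.
- Grade 5: death.

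**Four events read against the rows.**

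1. Severe pain that limits self-care, managed at home. It meets the Grade 3 heading and descriptor, so Grade 3 without difficulty.
2. Anaphylaxis with threat to life. It meets the Grade 4 heading, so Grade 4 without difficulty.
3. A mild or moderate event admitted for observation. The Grade 1 and Grade 2 rows say nothing about admission, so it can be graded 1 or 2.
4. A severe infection admitted for several days and never life-threatening. It meets the Grade 3 heading, fails the Grade 3 descriptor because of the admission, and does not meet the Grade 4 heading. The minimal, local or non-invasive treatment of Grade 2 does not describe it either.

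Only the fourth event meets the contradiction. A rater who follows the heading records Grade 3. A rater who follows the descriptor must look elsewhere, and the nearest place is Grade 4, whose descriptor on the need for immediate treatment an urgent admission could satisfy.

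**Where the grade goes next.**

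- Maximum-severity summary (section 15.3.6): the fourth event is counted in row 3 or row 4 according to the rater's reading.
- Seriousness: an admission that meets section 16.4 is serious at either grade, so nothing changes. Section 16.4 also lists admissions for surgery or tests among those not regarded as serious. If a severe event of that kind were moved to Grade 4, section 16.3 would make it serious and the two sections would disagree.
- Primary efficacy analysis: it does not use the grade.

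**Number of events affected.** It cannot be derived. The protocol gives no expected rate of hospitalised events, and sections 13.1 and 16.2 report that no significant adverse events were seen in earlier trials.

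**The case against.** The strongest reply is that the table does not govern. Section 16.3 says grading follows CTCAE v4.0 and presents the table as an example of it. A trained rater can go to the named scale, and the Grade 3 heading already covers the event. The Grade 2 row is also garbled, so the Grade 3 clause may be no more than a translation slip, although the document cannot confirm that. This reply stands as far as it limits the consequence. It does not make the row harmless, because the table is the only grading text the protocol prints and it contradicts itself within one row.

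A reader might infer more than the document supports:

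- *That such an event fits no grade at all.* The Grade 3 heading fits it. What is missing is a grade that fits without contradiction.
- *That every hospitalised, non-life-threatening event is misgraded.* Grades 1 and 2 carry no hospitalisation condition, so only severe events are affected.
- *That the between-group severity table will be wrong or biased.* The trial is double-blind and the same wording applies in both arms. Inconsistent grading is a risk; a bias between arms is not shown.
- *That the most important non-fatal events are lost.* Section 16.4 captures them as serious, the action code records the admission, and section 15.3.6 counts serious events separately from the severity summary.
- *That the number affected can be stated.* An assumed rate of 1–3% of 200 women would give 0.01 × 200 = 2 to 0.03 × 200 = 6 admitted events. Nothing in the protocol supports that rate, and the count would include mild and moderate events that the contradiction does not touch.

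**Conclusion.** The point holds as a minor internal contradiction. The Grade 3 descriptor in section 16.3 excludes what its heading includes, and a severe, hospitalised, non-life-threatening event may be recorded as Grade 3 by one rater and Grade 4 by another. The effect is confined to the upper rows of the maximum-severity summary and to the link between Grade 4 and seriousness. No event count and no bias between arms can be derived, serious-event capture is preserved, and efficacy is unaffected.

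The conclusion rests on reading the printed table as guidance that raters will use. If all sites grade directly from CTCAE v4.0, the practical effect would depend on that scale's own wording, which the protocol does not reproduce. The row would still need correcting.

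**What to change.** In the Grade 3 row of section 16.3, remove the exclusion of hospitalisation and prolonged stay, so that the descriptor agrees with its own heading, and check the row against the CTCAE v4.0 scale that the section names. Add one sentence stating that the severity grade and seriousness under section 16.4 are assessed separately. Check the grade of any severe hospitalised event already recorded.

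Do not replace the clause with a rule that hospitalisation by itself makes an event Grade 3. That would let admission set the severity of mild and moderate events and bring back the same mixing of severity and seriousness.

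The cost is a short text correction in the protocol and in any case report form guidance that repeats the table, plus a review of what is likely to be a small number of records. No analysis, sample size or endpoint changes.

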### 16.4 Evaluation methods and evaluation criteria for serious adverse events

Serious AEs (ADRs) refer to any of the following adverse events or adverse drug reactions occurring at any dose of the Investigational Product used in the test:

1) In case of death or danger to life

2) If you need to stay in the hospital or need to extend the length of stay

3) Permanent or significant failure or degradation of function

4) If the fetus has malformed or abnormalities

In addition, the following items are not regarded as serious adverse reaction.

1) If you do not need hospitalization due to voluntary will

2) If you are admitted to the hospital due to surgeries, tests, etc.

All adverse events should be recorded in the supporting documentation and case record, and the same adverse reaction terms should be used. If a "serious adverse event" occurs during the study period, report it to the Institutional Review Board to decide whether to continue or discontinue the study.

If serious adverse drug reactions occur during the course of a clinical trial, the test taker will cease part or all of the trials for the clinical trial drug and report it immediately to the trial investigator and the trial sponsor. The investigator should report to the clinical trial committee and test sponsor by telephone or facsimile within 24 hours of occurrence or at least the next day. In addition, within 7 days after the occurrence of a serious adverse event, additional reports should be included with the documentation in details. The sponsor should promptly report any adverse events that have not been reported to other relevant researchers or jury members in accordance with the drug clinical trial management standards.

1. Rapid Reporting: In the event of a serious adverse event occurring during the course of a clinical trial, regardless of whether it is related to the Investigational Product, the investigator or the investigator should contact the Clinical Trials Commission within 24 hours (Or the person in charge) of the clinical trial entrusted institution entrusted by BioLeaders or CRO.

* Monitor Person (or Person in Charge): Attachment 3. Note for Monitor

2. Detailed Reporting: Additional reporting should be made to the documentation within 5 days after the occurrence of the serious adverse event.

3. Tracking adverse events

The investigator or the person in charge should observe the clinical symptoms of the adverse reaction until the symptom subsides and the abnormal clinical test returns to baseline or a satisfactory explanation for the observed change is obtained. In addition, the progress of the adverse reaction should be reported to the person in charge.

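### Section 16.4 makes a needed hospital stay serious, then exempts any admission for surgery or tests without a qualifier, so the same unplanned admission is both serious and not serious

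*Protocol*

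**What the plan says.** **The definition.** Protocol section 16.4 says that serious events "refer to any of the following adverse events or adverse drug reactions occurring at any dose of the Investigational Product", so meeting one item on the list is enough and no severity grade is required. The second item on the list is "2) If you need to stay in the hospital or need to extend the length of stay".

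**The exemption.** The same section continues: "In addition, the following items are not regarded as serious adverse reaction". Two items follow. The first concerns voluntary admission where a hospital stay is not needed. The second is "2) If you are admitted to the hospital due to surgeries, tests, etc".

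**Related provisions.**
- Section 16.3 grades severity by CTCAE v4.0 and adds "but Grade 4 or 5 is considered a serious adverse event".
- Section 16.3 includes worsening of an existing condition among adverse events.
- Section 16.3, item 3, provides an action code, "5 = Hospitalization / prolonged hospitalization".
- Section 16.4 also requires that "All adverse events should be recorded in the supporting documentation and case record".

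**The concern.** The exemption is not confined to elective admissions, procedures scheduled before enrolment, or stable pre-existing disease, and its closing word leaves it open-ended. A woman admitted unexpectedly for an operation on a new event, or for urgent investigation of an unexplained reaction after dosing, satisfies the hospital-stay criterion and the exemption together. The protocol does not say which one wins.

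Three things depend on the serious label:
- the 24-hour report to the review body and the sponsor (16.4);
- the referral to the review board on whether the study continues (16.4);
- the serious-event numbers summarised by group and the between-group comparison of event incidence (15.3.6, item 1).

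A site that applies the exemption as written would miss all three for that event. A site that applies the criterion would not. The same event could then be classified differently across the six sites named in the outline.

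**Working it through.** No arithmetic applies. The point turns on wording and depends on no rate, error level or sample size. The check is to take each type of admission through the text of 16.3 and 16.4.

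| Admission | Hospital-stay criterion (16.4) | Surgery/tests exemption (16.4) | Result as written |
| --- | --- | --- | --- |
| Medical treatment of a new event, no operation or test as the reason | met | not met | serious |
| Surgery or tests planned before consent, condition unchanged | not an adverse event under 16.3, so the criterion is not engaged | met | not serious, no conflict |
| Unplanned surgery for a new or worsened event | met | met | contradictory |
| Unplanned diagnostic work-up of a new or worsened event | met | met | contradictory |
| Unplanned surgery for a life-threatening or disabling event | met, and another 16.4 criterion is met too | met | serious by another criterion, but precedence is not stated |

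**Step 1: locate the conflict.** It lies in rows 3 and 4 and, because precedence is not stated, partly in row 5. Row 2 is the case an exemption of this kind usually serves, and there it does no harm. The wording reaches well beyond row 2.

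**Step 2: look for a resolving rule elsewhere.** Section 15.3.6 lists serious events for summary but does not define them. Section 16.3 states a grade rule but says nothing about the exemption. Neither settles rows 3 and 4.

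**Step 3: check whether the grade rule in 16.3 widens the gap.** It does not. It makes Grade 4 or 5 sufficient for seriousness, and 16.4 makes any listed criterion sufficient at any grade. Two sufficient conditions add together, so the grade rule can only add serious events. If anything it offers a second route to the label for Grade 4 or 5 events in row 5, which leaves the conflict most exposed for events of Grade 3 or below.

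**Step 4: check what is lost.** All adverse events are recorded whether or not they are serious, and hospitalisation has its own action code. The admission therefore remains visible in the case record. What is lost is the classification and whatever depends on it.

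**The case against.** **The exemption may have been meant narrowly.** The best defence is that the two exempted items belong together and separate voluntary or procedural admissions from those caused by an adverse event. On that reading, emergency surgery for a new event stays under the hospital-stay criterion. The neighbouring item is visibly garbled, so a qualifier lost in translation is plausible. This stands as a guess at intent. The document contains no such qualifier, and sites apply what is written.

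**The lead-in speaks of reactions, not events.** One could argue that only reactions are exempted. However, 16.4 opens by treating serious events and serious drug reactions as one category, so the choice of word does not resolve the overlap.

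**Such events do not disappear.** This stands. They are recorded and coded, admissions for medical treatment remain serious, and fatal, life-threatening or disabling events meet other criteria.

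**Stronger readings that the documents do not support.**
- A reader might infer that 16.3 restricts seriousness to Grade 4 or 5, so that a severe but not life-threatening event leading to admission is non-serious under 16.3. The sentence contains no such restriction, and 16.4 sets no grade threshold.
- A reader might infer that the Grade 3 row, worded "without hospitalization or extension of length of stay", removes hospitalised events from the serious category. The table is presented as a generic CTCAE example, and the seriousness criteria do not refer to grades. The row is awkward but cannot take the serious label away.
- A reader might want to express the effect as a percentage of each arm's serious events. The protocol gives no serious-event rate for this trial. Section 6.4 reports none in the earlier 99-subject study, so any percentage would only restate an assumed denominator.
- A reader might cite cone resection after lesion progression as a common example. Section 12.2.15 places that diagnosis at the final visit and ends the patient's participation if progression is found, so it is weak support.

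**Conclusion.** The point holds as an internal contradiction in section 16.4, and it should be corrected. The hospital-stay criterion and the surgery/tests exemption cannot both be applied to an unplanned admission for an operation or work-up of a new or worsened event, and nothing else in the protocol decides between them. This is a rule stated too broadly, not a detail that could be left to a later document.

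Its size is limited to that class of admission. For those events the exposure is the serious classification, the 24-hour report, the review-board referral and the serious-event counts by arm. The adverse-event record itself is not lost. The number of events affected cannot be derived from the protocol. The conclusion assumes only that sites follow the text as written. If the sponsor always intended planned procedures alone, the text still has to say so.

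**What to change.** In section 16.4, reconcile the two items by limiting the exemption to admissions for surgery or tests that were planned before consent, for a pre-existing condition that has not worsened on study. Any other admission that an adverse event makes necessary then stays under the hospital-stay criterion, whatever is done in hospital. Carry the same wording into the instructions for the serious-event form.

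The grade rule in 16.3 and the Grade 3 row need no change for this purpose. A short clause confirming that Grade 4 or 5 is an additional trigger alongside the 16.4 list would prevent the misreading described above, but it is optional.

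The cost is a few words, with possibly a few more serious-event reports. Design, sample size and primary analysis are untouched.
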